## Abstract

**Background:**

Patient-ventilator asynchrony is a common problem in mechanically ventilated patients with acute respiratory failure. It is assumed that asynchronies worsen lung function and prolong the duration of mechanical ventilation (MV). Neurally Adjusted Ventilatory Assist (NAVA) is a novel approach to MV based on neural respiratory center output that is able to trigger, cycle, and regulate the ventilatory cycle. We hypothesized that the use of NAVA compared to conventional lung-protective MV will result in a reduction of the duration of MV. It is further hypothesized that NAVA compared to conventional lung-protective MV will result in a decrease in the length of ICU and hospital stay, and mortality.

**Methods/design:**

This is a prospective, multicenter, randomized controlled trial in 306 mechanically ventilated patients with acute respiratory failure from several etiologies. Only patients ventilated for less than 5 days, and who are expected to require prolonged MV for an additional 72 h or more and are able to breathe spontaneously, will be considered for enrollment. Eligible patients will be randomly allocated to two ventilatory arms: (1) conventional lung-protective MV (*n* = 153) and conventional lung-protective MV with NAVA (*n* = 153). Primary outcome is the number of ventilator-free days, defined as days alive and free from MV at day 28 after endotracheal intubation. Secondary outcomes are total length of MV, and ICU and hospital mortality.

**Discussion:**

This is the first randomized clinical trial examining, on a multicenter scale, the beneficial effects of NAVA in reducing the dependency on MV of patients with acute respiratory failure.

**Trial registration:**

ClinicalTrials.gov website (NCT01730794). Registered on 15 November 2012.

**Electronic supplementary material:**

The online version of this article (doi:10.1186/s13063-016-1625-5) contains supplementary material, which is available to authorized users.

## Background

The act of taking a breath is controlled by the respiratory center of the brain, which decides the characteristics of each breath, its timing, and its size. The respiratory center sends a signal along the phrenic nerve that excites the diaphragmatic muscle cells, leading to muscle contraction and descent of the diaphragmatic dome. As a result, the pressure in the airway drops causing an inflow of air into the lungs. Patient-ventilator asynchrony is a common problem in mechanically ventilated patients with acute respiratory failure (ARF). Asynchrony has been frequently documented in both volume and pressure assist/control (A/C) as well as pressure support ventilation. Two recent clinical studies have reported an increased length of mechanical ventilation (MV) requirement in patients with an Asynchrony Index (AI) ≥ 10 % versus those with an AI < 10 %. AI is defined as the ratio between number of asynchronies per minute/total respiratory rate × 100. In one study, patients with an AI ≥ 10 % required 25.5 days of ventilatory support versus 7.5 days in those with an AI < 10 % [1], while in the other study the number of ventilator-free days (VFDs) was 21 days (AI ≥ 10 %) versus 25 (AI < 10 %) [2]. In a more recent study in 50 patients all triggering the ventilator, every patient had multiple periods during the day where the AI was over 5 % and some had an AI as high as 40 % [3]. Of even greater concern is the fact the clinicians have a very difficult time identifying the presence of asynchrony and determining the AI at the bedside [4].

A new mode of ventilation, Neurally Adjusted Ventilatory Assist (NAVA) has been recently introduced [5–16]. With NAVA, the electrical activity of the diaphragm (Edi) is captured, fed to the ventilator and used to assist the patient’s breathing in synchrony with, and in proportion to, the patient’s own efforts regardless of patient category or size. NAVA triggers, cycles and regulates gas delivery based on the diaphragmatic electromyography (EMG) signal via a specially designed nasogastric tube (Edi). As the work of the ventilator and the diaphragm is controlled by the same signal, coupling between the diaphragm and the ventilator is synchronized simultaneously. As a result, synchrony should be markedly improved with NAVA since neither air leaks nor auto-positive end-expiratory pressure (auto-PEEP) should affect the ability of the ventilator to trigger, deliver gas or cycle.

We hypothesized that the use of NAVA will improve patient-ventilator interaction, will make the transition to spontaneous breathing much quicker and easier, and will result in an increase in VFDs in patients with ARF when compared to conventional lung-protective MV. If our hypothesis is correct, the use of NAVA will decrease the duration of MV, the length of intensive care unit (ICU) stay, ventilator-associated complications, and has the potential to increase overall survival of patients with ARF.

## Methods/design

### Justification of the study

Patient-ventilator asynchrony is a common problem in mechanically ventilated patients with ARF who are receiving assisted ventilation. Based on new data, all patients managed with conventional modes of MV have an AI > 5 % at various points during the day [3]. NAVA is a unique approach to MV based on neural respiratory output, providing a smooth transition to natural breathing. NAVA better assures that the patient’s breathing is in synchrony with, and in proportion to, the patient’s own efforts, regardless of patient category or size.

We justify the need for our study based on the fact that NAVA can provide a smooth transition to natural breathing. We hypothesized that the use of NAVA compared to conventional lung-protective MV will result in a decrease in the number of days of MV. It is further hypothesized that NAVA will result in a decrease in the length of ICU and hospital stay. The goal of this study is to compare the ability of NAVA versus conventional lung-protective MV to provide invasive ventilatory support during ARF in adults who are expected to require ventilatory support for at least 72 h.

### Study design

This study is a prospective, multicenter, randomized controlled, clinical trial in 306 adult patients (male and female) with ARF admitted to a network of 18 ICUs from university and community hospitals in Spain (Appendix 1).

The trial has been designed in accordance with the fundamental principles established in the Declaration of Helsinki, the Convention of the European Council related to human rights and biomedicine, and the Universal Declaration of UNESCO on the human genome and human rights, and within the requirements established by the Spanish legislation (Law 14/2007, Law 15/1999) in the field of biomedical research, the protection of personal data, and bioethics. The study was registered on 15 November 2012 at https://clinicaltrials.gov/ct2/show/NCT01730794 with the identification number NCT01730794. The study was approved by a referral Ethics Committee (Hospital Clínico Universitario de Valencia, Valencia, Spain) and the Institutional Review Boards (IRBs) of all participating hospitals (Additional file 1). For inclusion into the study, signed written informed consent from the patient or the patient’s personal legal representative will be obtained (Additional file 2). See Additional file 3 for the Standard Protocol Items: Recommendations for Interventional Trials (SPIRIT) checklist of the study protocol.

### Study population

To be eligible for inclusion into this study (day 0), each patient must fulfill the following inclusion criteria during screening and prior to enrollment into the trial: be aged 18 years or older, have hypoxemic or hypercapnic ARF, be intubated and mechanically ventilated for less than 5 days but expected to be ventilated for at least 72 h, and be able to spontaneously trigger the ventilator. Patients will be excluded from study participation if any of the following criteria are present: moderate or severe acute respiratory distress syndrome (ARDS) [17], the presence of three or more organ system failures, require noninvasive ventilation, be unable to spontaneously breathe, or have a poor short-term prognosis (defined as a high risk of death in the next 3 months), neuromuscular or neurological disease, lack of informed consent, and any medical/surgical contraindication.

### Enrollment into the study and randomization

Although the calculation of AI is not mandatory for patient enrollment after patient consent, it is recommended to perform (and save) a 1- to 15-min tracing recording of the patients’ pressure and flow waveforms during the mode of MV that they were receiving at the time of randomization. At the end of the study, in a randomly selected 10 % of enrolled patients, the AI will be calculated based on the following: (1) number of missed triggers (an airway pressure decrease of at least 0.5 cmH_2_O that does not result in triggering of the ventilator), (2) number of double triggers (two consecutive breaths without an exhalation between them), (3) auto-triggers (ventilator triggering to inspiration without a decrease in airway pressure of at least 0.5 cmH_2_O), (4) short inspiratory time (inspiratory time less than half of the mean inspiratory time), and (5) long inspiratory time (inspiratory time more than twice the mean inspiratory time). We will determine the AI using the formula from Thille et al. [1]:$$ \mathrm{AI}\ \left(\%\right) = \mathrm{number}\ \mathrm{of}\ \mathrm{asynchrony}\ \mathrm{events}/\mathrm{total}\ \mathrm{respiratory}\ \mathrm{rate}\ \left(\mathrm{which}\ \mathrm{includes}\ \mathrm{ventilatory}\ \mathrm{cycles} + \mathrm{wasted}\ \mathrm{efforts}\right) \times 100. $$

Thille et al. placed a pressure transducer and pneumotachograph at the airway and recorded breaths for 30 min. This is impractical to do as an entry criterion for a multicenter randomized controlled trial. However, all possible efforts will be made to record representative waveform tracings using the Servo-tracker software, or the Servo-i ventilator PCMCIA recording cards, or by any other means during a 1- to 15-min period of the ventilatory tracing before enrollment.

Eligible and informed consented patients who are expected to be ventilated for at least 72 h will be enrolled and randomly allocated to two arms: (1) NAVA or (2) conventional lung-protective MV, within the first 5 days (120 h) after endotracheal intubation (Fig. 1).

**Fig. 1 Fig1:**
[figure not shown]
Study design diagram

The randomization list was done by the statistician of the study ([name]), according to a computer-generated random number table based on a 1:1 allocation. This list was generated when the investigators and all Ethics Committees and IRBs of the participating centers had approved the study design. Randomization is stratified by center to ensure an equal distribution of patients in each arm by each ICU. Patients are randomly allocated to the two arms of the study (NAVA or no NAVA) by the clinical investigator in each participating ICU according to the precise written allocation contained inside a prenumbered, opaque, sealed envelope sent in blocks of ten envelopes to each participating ICU. Investigators must respect the numerical sequence of the envelopes. Only two members of the Trial Management Team have access to the randomization list: the project manager and the statistician. They keep the randomization list in their private office at the Research Unit of the Coordinating Center. The coordinating center does not enroll patients.

Our study characteristics do not allow the blinding of investigators to the intervention being tested. Once a participating ICU randomizes a patient, their investigators must contact the project manager of the study to inform and confirm the randomization number, the correct sequence of the prenumbered envelope, and the intervention arm. Screening, enrollment, randomization, treatment initiation, and follow-up of randomized patients is performed by the investigators and attending physicians in each participating ICU. Subsequent blocks of ten envelopes are sent to those participating ICUs with high enrollment rates. Participating clinicians do not know whether the pattern of stratification by center is for every 10, 20, or more envelopes during the study period.

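### The coordinating center is contacted only after the envelope is opened, so the described check cannot detect an opened envelope being reassigned to another patient

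*Protocol article*

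**What the plan says.** The procedure is in the protocol article, under Enrollment into the study and randomization, in the text after Fig. 1.

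- **Who allocates:** "Patients are randomly allocated to the two arms of the study (NAVA or no NAVA) by the clinical investigator in each participating ICU".
- **With what:** the allocation is "contained inside a prenumbered, opaque, sealed envelope sent in blocks of ten envelopes to each participating ICU".
- **Order of events:** "Once a participating ICU randomizes a patient, their investigators must contact the project manager of the study to inform and confirm the randomization number". The same sentence adds "the correct sequence of the prenumbered envelope, and the intervention arm".
- **Safeguards:** "Investigators must respect the numerical sequence of the envelopes", and "Only two members of the Trial Management Team have access to the randomization list: the project manager and the statistician". The person who receives the report can therefore compare it with the list.
- **Blinding:** "Our study characteristics do not allow the blinding of investigators to the intervention being tested".

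The same section gives screening, enrollment, randomization, start of treatment and follow-up to the investigators and attending physicians of each ICU. Under Sample size calculations and interim analysis, the article limits the analysis to patients who were enrolled and randomized.

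**The concern.** When allocation is open once the envelope is unsealed, what protects the comparison is that a patient is irrevocably in the trial before anyone sees the arm. Here the outside party hears of the patient only afterwards. The clinician who has just read the arm is also the one who judged eligibility, and two of the criteria under Study population call for judgement: the expectation of at least 72 h of ventilation, and a poor short-term prognosis. A patient could be reclassified as unsuitable once the arm is known, and the envelope used for the next one.

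At stake is the comparability of the arms at entry. If patients with a worse outlook were passed over more often in one arm, ventilator-free days would differ between arms without any treatment effect. Intention-to-treat analysis would not correct this, because the passed-over patient has no randomization record.

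**Working it through.** The plan states no figure on this point, so the main check is to follow possible departures through the described procedure.

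**1. What the check detects**

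| Event after opening | Number | Sequence | Arm against list | Detected? |
|---|---|---|---|---|
| Patient dropped, envelope not used again | missing | gap at the next report | not applicable | Yes |
| Arm changed from that in the envelope | in order | in order | mismatch | Yes |
| Envelope taken out of order | wrong | broken | may match | Yes |
| Opened for patient A, A passed over, reported for patient B | in order | in order | match | No |

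The last row passes because all three confirmed items belong to the envelope. None identifies the patient for whom it was opened.

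**2. Does patient A appear in the analysis?** No. The analysis covers enrolled and randomized patients, and A has no number.

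**3. How large could the effect be?** This is an illustration.

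Inputs from the article (Sample size calculations and interim analysis): SD 6 ventilator-free days, 153 patients per arm, planned effect 2 days.

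Assumptions, not in the article:
- There is no true effect, and outcomes are normal.
- When the opened envelope says NAVA, a patient with below-median prognosis is passed over with probability *f*, and the envelope goes to the next patient.
- The prognosis the clinician perceives correlates *r* with the outcome.

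Mean shift in standardized prognosis among those kept: *k* = *f* × 0.3989 / (1 − *f*/2), where 0.3989 is the standard normal density at zero.

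False difference: *d* = 6 × *r* × *k*.

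Standard error of the difference: 6 × √(2/153) = 0.686.

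Type I error (two-sided, 0.05): P(Z > 1.96 − *d*/0.686) + P(Z < −1.96 − *d*/0.686).

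Passed-over patients needed to fill 153 NAVA places: 153 × (*f*/2) / (1 − *f*/2).

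| *f* | *k* | Passed over | *d*, *r* = 0.3 | *d*, *r* = 0.5 | Type I error |
|---|---|---|---|---|---|
| 0.1 | 0.042 | 8 | 0.08 | 0.13 | 5.1 to 5.4 % |
| 0.2 | 0.089 | 17 | 0.16 | 0.27 | 5.6 to 6.7 % |
| 0.3 | 0.141 | 27 | 0.25 | 0.42 | 6.6 to 9.4 % |

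Example, *f* = 0.3 and *r* = 0.5: *k* = 0.3 × 0.3989 / 0.85 = 0.141; *d* = 6 × 0.5 × 0.141 = 0.42; *d*/0.686 = 0.616; type I error = P(Z > 1.344) + P(Z < −2.576) = 0.094.

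Simulation of the same model (4,000 trials per setting) gave 0.07 to 0.43 days and a type I error of about 5 to 10 %, in agreement within simulation error. The largest false difference is 0.42/2 = 21 % of the planned effect, and it takes about 27 passed-over patients in one arm. Passing over patients when the envelope says control would push the result the other way.

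**The case against.** Sequentially numbered, opaque, sealed envelopes with central confirmation are a recognized way to conceal allocation, and their use contradicts nothing in the article. That stands: the point is a weak order of steps in a sound method.

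The article also places eligibility and consent before allocation, and Table 1 puts the consent form at screening. If that order is kept, a passed-over patient leaves a signed consent without a randomization number, and a swap needs a second eligible, consented patient. This makes reassignment harder and gives an audit something to find. It does not close the gap, because the described confirmation does not compare consents with envelopes.

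The article is condensed. It refers to an additional file and, under Trial organization, to an investigator manual and auditing. Signed envelopes or a screening log may be set out there, so their absence here is not the finding. The finding rests on what the article does state: contact follows randomization and covers number, sequence and arm. A screening log or signed envelope would narrow the gap but would not change that order.

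A reader might go further and infer that late allocations can be guessed, since envelopes arrive in tens, allocation is stratified by ICU and past arms are visible. The documents do not support this. Ten is the number sent at a time; balance within each ten is nowhere stated. The article also says that clinicians do not know whether the pattern runs over 10, 20 or more envelopes.

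**Conclusion.** The point holds in limited form. The described check protects the order of the envelopes and the arm each contains. It does not protect the link between an envelope and the patient for whom it was opened. In an unblinded trial with local envelopes, an opened envelope can be reassigned to another eligible patient and pass every check described.

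A reader might infer that any patient can be dropped or swapped without trace. That is too broad: a discarded envelope leaves a gap in the numbers, and an altered arm disagrees with the list. Only reassignment with the envelope kept for the next patient escapes. Nor is there evidence that it occurs.

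The size is unknown. Under the assumptions shown, the false difference is 0.08 to 0.42 ventilator-free days and the type I error about 5 to 9 %. That is modest beside a planned effect of 2 days, but it is systematic and cannot be removed in the analysis. The change is worth making because it is cheap.

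**What to change.** For all remaining patients, make the existing contact before the envelope is opened:

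1. The investigator registers the consented, eligible patient with the project manager: study ID, confirmation of eligibility, date and time. Out of hours, a time-stamped message is enough.
2. The investigator then opens the next envelope in sequence and reports number and arm, as now.
3. The coordinating center reconciles every numbered envelope with its pre-registered patient and follows up any registration without an envelope, or envelope without a registration.

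The cost is a short extra step and possibly a short wait before randomization. The time-stamped message means that no patient near the 120 h enrollment limit need be lost because the office is closed. The randomization list and the envelopes already sent stay as they are; no change of block size is needed.

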### Ventilatory management

In the conventional lung-protective MV group, patients will be ventilated using either volume assist/control (A/C), pressure A/C, pressure support (PS), pressure-regulated volume control (PRVC), or volume support (VS) at the discretion of the medical team with tidal volumes (VT) in the 4 to 8 ml/kg predicted body weight (PBW) range and plateau pressure or pressure (control or support) level setting of 30 cmH_2_O or less. During A/C the backup rate must be set to insure that more than 90 % of breaths are triggered by the patient. In the weaning phase of ventilatory support, a VT of up to 10 ml/kg will be acceptable. Volume and pressure ventilation should be optimized by careful adjustment of peak flow and inspiratory time (volume ventilation), and rise time and termination criteria (pressure ventilation) to insure maximum patient-ventilator synchrony. In volume ventilation, inspiratory time should be less than 1.0 s and peak flow should be high enough to avoid any concavity during the initial part of inspiration. In pressure ventilation, rise time should also be set to avoid any concavity during the initial part of inspiration, and the patient’s neural inspiratory time and the ventilator’s inspiratory time should end simultaneously by careful setting of inspiratory time or termination criteria. Trigger sensitivity should be set to insure the minimal effort that does not result in auto-triggering.

For the purpose of this study, patients allocated to the NAVA group will be ventilated with Servo-i ventilators (Maquet-Getinge, Solna, Sweden). One NAVA catheter size will be used for this study: Edi catheter 16 Fr (Maquet-Getinge, Solna, Sweden). For details on guidelines for positioning the Edi Catheter, initial NAVA settings, and subsequent adjustments of NAVA, see Additional file 4. The NAVA level will be set initially at zero, then the maximum Edi will be determined as the average level over the next at least three to five breaths without ventilatory support but with 5 cmH_2_O of PEEP. The actual NAVA level will then be titrated by the clinician to achieve the following: (1) an Edi equal to approximately 50 % of the maximum Edi, (2) an average VT of between 4 to 8 ml/kg PBW, and (3) an average respiratory rate of between 15 and 40 per min. In addition, the trigger sensitivity should be set as sensitive as possible without causing auto-triggering and the maximum pressure limit in NAVA should be set at 40 cmH_2_O. The NAVA catheter should be changed every 5 days.

In both groups, PEEP will be set in hypoxemic ventilatory failure patients at a minimum of 5 cmH_2_O. Since none of these patients will have moderate or severe ARDS, it is expected that PEEP levels in most patients will be set between 5 and 15 cmH_2_O based on the clinical judgment of the attending physician. The primary exception to this is patients with marked obesity who may require PEEP levels of up to 15 to 20 cmH_2_O. However, a high-PEEP-low-FiO_2_ approach is expected with all of these patients. In chronic obstructive pulmonary disease (COPD) patients, PEEP will be set to offset auto-PEEP. That is, PEEP will be increased to the level that insures that the vast majority of patient efforts result in triggering of the ventilator. In congestive heart failure patients, PEEP will be set at 8 to 12 cmH_2_O based on the patient’s hemodynamic status.

In both arms, FiO_2_ will be set to insure a PaO_2_ of 60 to 80 mmHg after the setting of PEEP. In patients who leave the ICU for any reason, the randomized approach should be continued during their travel. Patients who require sedation or anesthesia for procedures should be placed back on the appropriately randomized mode as soon as they are able to breathe spontaneously. Throughout this study, the applied VT will be based on the patients’ PBW. The following formulas are to be used to calculate PBW (kg):$$ \mathrm{P}\mathrm{B}\mathrm{W} = 50.0 + \left[0.91 \times \left(\mathrm{height}\ \mathrm{in}\ \mathrm{cm} - 152\right)\right]\ \mathrm{f}\mathrm{o}\mathrm{r}\ \mathrm{men}, $$

and$$ \mathrm{P}\mathrm{B}\mathrm{W} = 45.5 + \left[0.91 \times \left(\mathrm{height}\ \mathrm{in}\ \mathrm{cm} - 152\right)\right]\ \mathrm{f}\mathrm{o}\mathrm{r}\ \mathrm{women}. $$

In all patients, weaning will be performed by a spontaneous breathing trial (SBT) [18]. Following extubation in both groups, noninvasive ventilation will be applied for 24 to 48 h if patients are over 65 years old, have COPD or congestive heart failure, have an ineffective cough and excessive secretions, have had at least one weaning failure, more than one comorbid condition, upper airway obstruction, or an APACHE II score > 12 on the day of extubation. In the control arm noninvasive PS will be applied, and in the NAVA arm noninvasive NAVA will be applied.

If, after 2 h post extubation, an FiO_2_ > 0.40 is required, patients will be maintained on continuous positive airway pressure (CPAP) at 10 cmH_2_O or bilevel positive airway pressure (BiPAP) at clinically determined settings with peak inspiratory pressure of 20 cmH_2_O or less via face mask until they are able to maintain a PaO_2_ > 60 mmHg on an FiO_2_ ≤ 0.40. If patients do not respond to CPAP/BiPAP within 2 h, reintubation for those considered failing should not be delayed. Patients in the NAVA group should not have the NAVA catheter removed until BiPAP or CPAP has been discontinued. If these patients are reintubated they are to return to NAVA.

